**Methods/Design:**

An open, multicentre and parallel randomized clinical trial with blinded assessment. 160 nursing home residents aged over 65 years and of both sexes will be identified to participate in the study. Participants will be centrally randomised and allocated to interventions (vibration or exercise group) by telephone. The vibration group will perform static/dynamic exercises (balance and resistance training) on a vibratory platform (Frequency: 30-35 Hz; Amplitude: 2-4 mm) over a six-week training period (3 sessions/week). The exercise group will perform the same exercise protocol but without a vibration stimuli platform. The primary outcome measure is the static/dynamic body balance. Secondary outcomes are muscle strength and, number of new falls. Follow-up measurements will be collected at 6 weeks and at 6 months after randomization. Efficacy will be analysed on an intention-to-treat (ITT) basis and 'per protocol'. The effects of the intervention will be evaluated using the "t" test, Mann-Witney test, or Chi-square test, depending on the type of outcome. The final analysis will be performed 6 weeks and 6 months after randomization.

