### Follow-up

All tests will be performed at baseline, at 6 weeks (at the end of the intervention

period), and 6 months after the end of the study (Figure 1).

Data concerning falls will be regularly collected from each nursing-home or from relatives if a participant moves to another address.

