##### • Number of falls

Any falls during the study will be recorded in a fall register developed specifically for the study.

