### Statistical methods

Efficacy will be analysed on an intention-to-treat (ITT) basis. Additionally, a 'per protocol' analysis will be performed. Missing values will be assigned the last available valid score. We will evaluate the effects of the intervention on each quantitative, qualitative and ordinal outcome using the "t" test, Mann-Witney test or the Chi-square test, depending on the type of outcome. The final analysis will be performed 6 weeks and 6 months after randomization. The number of falls over the 6-month period will be recorded.

Changes in body balance and muscle performance will be analysed 6 weeks and 6 months after starting the study using a two-way analysis of variance (ANOVA). Factors included will be the group (vibration or exercise group) and the time (at baseline and after six weeks of intervention), and the interaction between them. The software used will be SPSS17.

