## Discussion

WBV training is a type of physical exercise in which people perform various exercises in a squat position on a platform device. Several studies have shown promising results using this intervention in walking capacity, speed of gait, body balance, and muscle strength in elder adults [33-40]. Only two trials have evaluated the feasibility of WBV in functional mobility and muscle performance in institutionalized older persons [24,25] to date. Both these trials were small and the variability of the study protocols, comparators, outcome measures and limitations in the studies design made it difficult to reach any definitive conclusions about the effectiveness of WBV in increasing functional capacity of older persons [41].

Our study design incorporates a significantly larger sample, implements randomization, allocation and blinded outcome assessment, and introduces a longer follow up than previous studies. We consider this design will reveal differences between the two study groups in balance and muscle strength, and secondarily, in preventing falls.

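### The tests fixed for number of falls ignore observed time, so the comparison is biased if follow-up differs between arms; a rate model would avoid this at little cost

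*Protocol article*

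**What the plan says.** All places are in the protocol article.

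- **Outcome.** The abstract (Methods/Design) states: "Secondary outcomes are muscle strength and, number of new falls". The section on number of falls adds: "Any falls during the study will be recorded in a fall register developed specifically for the study". No rate, person-time or faller definition is given.
- **Tests.** Statistical methods: "We will evaluate the effects of the intervention on each quantitative, qualitative and ordinal outcome using the 't' test, Mann-Witney test or the Chi-square test", chosen by type of outcome. The only other model there is limited to other outcomes: "Changes in body balance and muscle performance will be analysed 6 weeks and 6 months after starting the study using a two-way analysis of variance".
- **Fall period.** Statistical methods: "The number of falls over the 6-month period will be recorded".
- **Missing data.** Statistical methods: "Missing values will be assigned the last available valid score". No outcome is exempted.
- **Fall collection.** Follow-up says that fall data come regularly from the homes, or from relatives once a participant has moved.
- **Sample size.** It rests on a 5-point Tinetti difference (SD 10), two-sided alpha 0.05, 80% power and 20% losses, giving 160 residents.
- **Expectation.** Discussion: "We consider this design will reveal differences between the two study groups in balance and muscle strength, and secondarily, in preventing falls".

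**The concern.** A fall count depends on how long the person was watched. None of the three named tests takes exposure time as an input: the t and Mann-Whitney tests would compare counts per person, and the chi-square test would compare proportions of fallers. A resident who dies or withdraws early contributes a short window but is treated as if observed throughout. Carrying a cumulative count forward has the same effect, because it adds zero falls after exit.

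If both arms lose the same observation time, the comparison remains fair. If they do not, the arm with less observation time shows fewer falls even when the two fall rates are equal. The article presents the trial as the first to evaluate this training for fall prevention, so the falls comparison is likely to be read with interest even though it is secondary.

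**Working it through.** **1. The plan's own figure.** Per arm, n = 2 × (1.96 + 0.84)² × (10/5)² = 62.8, so 63. Dividing by 0.80 for 20% losses gives 79 per arm, 158 in total. The t-distribution version gives 64 per arm, then 64/0.80 = 80 per arm and 160 in total, as stated. The figure reproduces, but only for the Tinetti test.

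**2. Assumptions for falls.** The documents give no fall rate, dispersion or loss rate for the fall register. Assumed: 1.5 falls per person-year, negative binomial dispersion 1, 80 per arm, a 6-month window, and early leavers exiting uniformly over it, so that each loses half the window on average.

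**3. Expected bias in the count ratio with no true effect.** If a fraction d leaves early, mean observed time is (1 − d/2) of the window. The apparent ratio is (1 − d₁/2)/(1 − d₀/2), with d₁ for the arm losing more:
- 20% vs 20%: 0.90/0.90 = 1.00
- 10% vs 30%: 0.85/0.95 = 0.895
- 10% vs 40%: 0.80/0.95 = 0.842
- 0% vs 40%: 0.80/1.00 = 0.80

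**4. Simulated type I error at nominal 5%.** The planned tests use counts or fallers; the rate model is negative binomial with log observed time as offset and dispersion set at its true value.

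| Early leavers | Planned tests: ratio | Planned tests: type I error | Rate model: ratio | Rate model: type I error |
|---|---|---|---|---|
| 20% vs 20% | 1.00 | 4.5–5.2% | 1.00 | 4.8% |
| 10% vs 30% | 0.90 | 6.5–7.2% | 1.00 | 5.2% |
| 0% vs 40% | 0.79 | 16–17% | 0.99 | 5.8% |

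These are 2,000 trials per row. Further sets of 5,000 trials gave 6.7–6.9% and 7.5–8.1% for 10% vs 30%, hence about 7–8% overall, and 10–11% for 10% vs 40%. The Monte Carlo standard error near 7% is √(0.07 × 0.93/2,000) = 0.6 percentage points for 2,000 trials.

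**5. Same mechanism with a true rate ratio of 0.7.** The crude ratio becomes 0.63 if the vibration arm has 30% leavers and the exercise arm 10%, and 0.78 if the imbalance is reversed. The rate model gives 0.71 and 0.69. With equal 20% loss, power is 19–26% for the planned tests and 27% for the rate model.

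**6. What 80 per arm can show on falls.** Var(log RR) = [(1/μ₀ + k) + (1/μ₁ + k)]/80, where μ₀ = rate × 0.5 year and μ₁ = μ₀ × RR; power = Φ(|log RR|/SE − 1.96). Example with rate 1.5, k = 1, RR 0.7: μ₀ = 0.75 and μ₁ = 0.525; variance = (2.333 + 2.905)/80 = 0.0655; SE = 0.256; power = Φ(0.357/0.256 − 1.96) = Φ(−0.57) = 29%. Over assumed rates of 1–2 per person-year and dispersion of 0.5–1.5, with no loss, power is 15–29% for a 25% reduction, 35–66% for a 40% reduction and 54–87% for a halving.

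**The case against.** The case for leaving the plan alone has real force on several points.

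- **Equal loss.** The tests hold their level when loss is balanced, and nothing in the documents points to imbalance: residents are randomized within each home and both arms do the same exercises for six weeks. A reader might infer that the planned tests are invalid as they stand, or that a harmful arm would look protective. The documents do not support that; the bias is conditional on unequal observation.
- **Moves.** Follow-up arranges for falls to be collected from relatives after a move. Transfers are therefore largely covered, and mainly death and withdrawal remain.
- **The 20% loss.** This figure belongs to the Tinetti calculation at the end of the intervention. Missing a test visit does not end fall registration, so it should not be read as the loss rate for falls.
- **Carry-forward.** The rule speaks of a score and does not name falls. It is tempting to say that the plan will carry fall counts forward; that is only one literal reading of a general rule.
- **Powering.** A secondary outcome need not be powered, and the Discussion sentence is framed as the authors' opinion and puts falls second. That a null result would be taken as proof of no effect is not something the documents say.
- **Derived variable.** A rank test on per-person rates could fit the wording, and a fuller document might define it.

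The last point is the weakest. The article defines the outcome as a number of falls and itself assigns every outcome to one of three tests, so this is a stated method rather than an omitted detail. The objection also rightly notes that an offset corrects for length of observation but not for exit that is related to fall risk, and that with equal loss the gain in power is small.

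**Conclusion.** The point holds as a conditional weakness with a cheap remedy. The stated tests compare falls without regard to time observed. With balanced loss this does no harm to the type I error (about 5%). With 10% versus 30% early leavers the apparent ratio is about 0.89 and the type I error about 7–8% when there is no true effect; more extreme imbalance does more damage. These sizes rest on an assumed 1.5 falls per person-year, dispersion 1, uniform exit times and loss that differs between arms, none of which the documents give.

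The Discussion sentence is a lesser matter. It expresses confidence about falls that no figure in the article supports, since the sample size rests on the Tinetti test alone. That is a wording issue, not a design error.

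**What to change.** In Statistical methods:
1. Analyse number of falls by negative binomial regression on group, with the log of observed time as offset, and report the rate ratio with its 95% CI.
2. State that the last-score rule does not apply to falls.
3. Record the date on which each resident's fall observation ends, and the reason.

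Time to first fall is optional.

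In the Discussion, reword the sentence to say that falls are a secondary outcome for which the trial was not sized.

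When defining the fall window, reconcile the two statements of the final time point: Follow-up has "period), and 6 months after the end of the study (Figure 1", while the abstract and Statistical methods count 6 months from randomization.

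The cost is one extra field in the fall register, slightly more data handling and a more modest claim; no additional participants are needed. The model still assumes that exit is not informative about fall risk, which should be acknowledged when results are reported. The change should be made before the data are unblinded, so that it is not post hoc.

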### Sample size

We calculated sample size was calculated assuming a difference of 5 points (SD 10) between the groups in the Tinetti test at the end of intervention. We considered a two-sided alpha level of 0.05, a statistical power of 80%, and 20% of losses [24,32]. The total number of estimated cases was 160 (80 in each group).

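### Baseline scores enter the planned analysis only through a group-by-time ANOVA; no analysis uses them as a covariate, so precision and protection from chance imbalance are given up at no saving

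*Protocol article*

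**What the plan says.** The Follow-up section provides for baseline measurement of every test: "All tests will be performed at baseline, at 6 weeks" and again at 6 months.

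The Statistical methods section then sets out two analyses.

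- The first is general to all outcomes: "We will evaluate the effects of the intervention on each quantitative, qualitative and ordinal outcome using the" t test, Mann-Whitney test or chi-square test, according to outcome type. These are two-group comparisons with no covariate.
- The second is specific to body balance and muscle performance: changes at 6 weeks and 6 months are to be analysed by two-way ANOVA with group, time and their interaction. The time levels listed are baseline and six weeks only.

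Baseline therefore appears once, as a level of the time factor. It is nowhere a covariate, and neither analysis is named as the main one for balance.

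The Sample size section plans the trial on "assuming a difference of 5 points (SD 10) between the groups in the Tinetti test at the end of intervention", which describes an end-of-intervention comparison, with 160 participants in total.

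**The concern.** The baseline score of the same test is usually the strongest predictor of the follow-up score, and here it is collected on everyone before training. The two planned comparisons treat it in the two extreme ways. The end-score test gives it a slope of 0. The group-by-time interaction, if fitted with a within-person term, is a comparison of change scores and gives it a slope of 1. ANCOVA estimates the slope from the data.

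Two things are at stake. One is precision: with equal SDs at both times, ANCOVA has a variance no larger than either planned comparison, apart from one degree of freedom. The other is chance imbalance at entry. It pushes the end-score estimate one way and the change estimate the other, so an imbalance would pull the two planned analyses apart, with no stated rule for choosing between them.

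The 6-month point is less well served than the 6-week point. The ANOVA sentence covers 6 months but its time levels do not, so the only clearly specified comparison at 6 months is the one that ignores baseline.

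**Working it through.** **Inputs from the protocol (Sample size).** "a difference of 5 points (SD 10"), "a two-sided alpha level of 0.05", "a statistical power of 80"%, 20% losses, and "The total number of estimated cases was 160 (80 in each group").

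**Inputs assumed.** The correlation r between baseline and follow-up score is not given, so a range from 0.3 to 0.8 is used. SDs are taken as equal at baseline and follow-up.

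**Step 1: reproduce the plan's figure.** For a two-sample t test with standardised difference 5/10 = 0.5, two-sided alpha 0.05 and 80% power, the requirement is 63.8, so 64 per arm. Allowing for losses, 64/(1 - 0.20) = 80 per arm, or 160 in total. The stated size is that of an unadjusted end-score comparison.

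**Step 2: effective SD of each analysis.**

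- End score: 10
- Change score (group-by-time interaction, repeated measures): 10 × sqrt(2(1 - r))
- ANCOVA: 10 × sqrt(1 - r²)

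ANCOVA against end score: the variance ratio is 1 - r², never above 1. ANCOVA against change: 2(1 - r) - (1 - r²) = (1 - r)², never below 0. So ANCOVA is at least as precise as either at every r. These ratios do not depend on the SD of 10.

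**Step 3: power at 64 per arm for 5 points (t-based).**

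| r | SD, change | SD, ANCOVA | Power, end score | Power, change | Power, ANCOVA |
|---|---|---|---|---|---|
| 0.3 | 11.83 | 9.54 | 80% | 66% | 84% |
| 0.5 | 10.00 | 8.66 | 80% | 80% | 90% |
| 0.7 | 7.75 | 7.14 | 80% | 95% | 98% |
| 0.8 | 6.32 | 6.00 | 80% | 99% | over 99% |

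Below r = 0.5 the change contrast does worse than ignoring baseline. Above 0.5 it recovers most of the gain: at r = 0.7 it has 95.2% against 97.6% for ANCOVA.

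**Step 4: difference detectable with 80% power at 64 per arm.** The end-score test detects 4.99 points. Multiplying by the SD ratios gives, at r = 0.7, 4.99 × 7.75/10 = 3.87 for the change contrast and 4.99 × 7.14/10 = 3.56 for ANCOVA. At r = 0.5 the figures are 4.99 and 4.32.

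**Step 5: effect of chance imbalance.** The standard error of the baseline difference between arms is 10 × sqrt(2/64) = 1.77 points, or 10 × sqrt(2/80) = 1.58 with all 80 per arm. Given an imbalance of one standard error, the expected shift is r × 1.77 in the end-score estimate and (r - 1) × 1.77 in the change estimate.

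| r | End score | Change | ANCOVA |
|---|---|---|---|
| 0.3 | +0.53 | -1.24 | 0 |
| 0.5 | +0.88 | -0.88 | 0 |
| 0.7 | +1.24 | -0.53 | 0 |
| 0.8 | +1.41 | -0.35 | 0 |

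At every r the two planned estimates are expected to differ by the full 1.77 points, against a target of 5.

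**The case against.** The strongest reply is that the plan does use baseline. The ANOVA is the one method assigned by name to balance and muscle performance, and its interaction, fitted as repeated measures, subtracts each person's baseline. That stands. A reader who sees only the t and Mann-Whitney sentence might infer that baseline is ignored altogether, and the next paragraph of the same section contradicts this. Judged against the change contrast, the gain from ANCOVA is modest at high correlation: 95.2% to 97.6% at r = 0.7. It is larger at lower correlation, and the protocol does not say whether the ANOVA has a within-person term; without one the pairing is lost.

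A reader might also infer that the trial is too small or its tests biased. Neither follows. The 160 reproduces for the unadjusted test, both comparisons are valid under randomisation, and ordinary chance imbalance is already reflected in their standard errors. The shifts in the working are conditional on an imbalance having occurred.

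The size of the gain rests on an assumed r and equal SDs; this too stands. At r = 0.3 the gain over the end-score test is only from 80% to 84%. The calculation also uses 64 per arm, whereas the intention-to-treat analysis with last value carried forward could include up to 80. That lowers the imbalance standard error to 1.58, and carrying values forward would alter the correlation itself. The ordering of the three methods holds for any n and r under equal SDs.

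Finally, covariates are often left to the analysis plan, which is not shown. Here, though, the article names the tests and the ANOVA factors, so the comment concerns a stated choice, not a gap.

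**Conclusion.** The point holds as a recommended improvement. No stated analysis uses baseline as a covariate, and ANCOVA on data already being collected is at least as precise as either planned comparison. Under the protocol's own inputs with 64 per arm, it raises power over the end-score test by about 4 percentage points at r = 0.3 and 10 at r = 0.5. Over the change contrast it gains about 18 points at r = 0.3, 10 at 0.5 and 2 at 0.7. It also removes, in expectation, the opposite-signed shifts that a baseline imbalance would put into the two planned estimates.

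The ordering is firm, given equal SDs. The amounts are conditional on a correlation that the document does not give and on the repeated-measures reading of the ANOVA. Nothing here invalidates the planned tests or the sample size.

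**What to change.** For Tinetti, Timed Up & Go and Sit-to-Stand, make the main analysis at 6 weeks and at 6 months a linear model of the follow-up score on group and the same test's baseline score. Report the adjusted mean difference with its 95% confidence interval.

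If a repeated-measures model is kept, use only the 6-week and 6-month scores as outcomes and enter baseline as a covariate. Baseline must then cease to be a level of time. Adding it as a covariate to the ANOVA as now written would place it on both sides of the model.

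The cost is a change of wording in Statistical methods. It needs no new data, visits or participants.

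### The group-by-time ANOVA names no resident term although residents are measured repeatedly; fitted as written, its treatment test is far too conservative and loses power

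*Protocol article*

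**What the plan says.** In the Protocol article, the second paragraph of Statistical methods states that "Changes in body balance and muscle performance will be analysed 6 weeks and 6 months after starting the study", and gives the model as follows: "using a two-way analysis of variance (ANOVA). Factors included will be the group (vibration or exercise group) and the time". The levels of time and the remaining term are "the time (at baseline and after six weeks of intervention), and the interaction between them". The section names no resident factor, within-resident error term, covariance structure or repeated-measures design.

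The Follow-up section shows that the levels of time are not separate samples: "All tests will be performed at baseline, at 6 weeks (at the end of the intervention" period), with a further visit at 6 months. Each resident therefore contributes one score per time point.

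Two other statements matter here. The first paragraph of Statistical methods also plans t, Mann-Whitney or chi-square tests of each outcome. The Sample size section rests on a simple between-group comparison, "assuming a difference of 5 points (SD 10) between the groups in the Tinetti test at the end of intervention".

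**The concern.** An ordinary two-way ANOVA with only group, time and their interaction treats the two scores of one resident as coming from two different people. Scores from the same person are normally positively correlated, so the model then has the wrong error variance for both of its group-related tests, in opposite directions.

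- **Group-by-time.** This compares the change between arms. Change within a person varies less than the model assumes, so the test divides by too large an error. It rejects too rarely when there is no effect and misses real effects.
- **Group main effect.** This compares the arms on the average of baseline and follow-up. The model counts twice as many independent people as there are, so the error is too small. The term also mixes a pre-treatment score into the comparison and, with two time points, estimates only half the effect (5/2 = 2.5 points).

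The interaction is the term that answers the trial's question, so the main thing at stake is lost power. Body balance is the primary outcome, and both this ANOVA and the simpler tests are planned for it. The two could disagree only because one of them uses the wrong error term.

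**Working it through.** **Inputs from the documents.** Difference 5 points, SD 10, two-sided alpha 0.05, power 80%, 20% losses, 160 residents (80 per arm), all from Sample size. Time levels baseline and 6 weeks, from Statistical methods.

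**Assumptions.** The within-resident correlation (rho) is not in the documents; 0.5 to 0.8 is taken as the main range and 0.2 to 0.9 as a wider one. The SD of 10 is taken to apply at both time points. The 80-per-arm figures allow for no dilution of the effect by carried-forward values.

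**1. The plan's own figure.** A two-sample t-test calculation needs 63.8, so 64 per arm; 64/0.8 = 80 per arm, total 160. This reproduces the plan, so 64 is the completer count per arm and 80 the randomised count.

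**2. Interaction test, fitted as written.** The contrast is the difference between arms in change.

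- SE assumed by the model: sqrt(4 × 10²/n) = 2.50 for n = 64 and 2.236 for n = 80.
- True SE: the assumed SE × sqrt(1 − rho).
- Actual type I error: 2 × [1 − Φ(1.96/sqrt(1 − rho))].
- Power as written: Φ[(5 − 1.96 × assumed SE)/true SE].
- Power with a within-resident error term: Φ[5/true SE − 1.96].

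Example, rho = 0.5 and n = 64: true SE = 2.50 × 0.707 = 1.768. Type I error = 2 × [1 − Φ(2.772)] = 0.56%. Power as written = Φ[(5 − 4.90)/1.768] = Φ(0.057) = 52%. Power with the right error = Φ(2.828 − 1.96) = Φ(0.868) = 81%.

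| rho | Type I error as written | Power, 64 per arm: as written / within-resident error | Power, 80 per arm: as written / within-resident error |
|---|---|---|---|
| 0.5 | 0.56% | 52% / 81% | 65% / 88% |
| 0.7 | 0.035% | 53% / 95% | 69% / 98% |
| 0.8 | 0.001% | 54% / 99% | 73% / 99.9% |

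At rho = 0.2 the type I error is 2.8%; at 0.9 it is effectively zero.

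**3. Group main effect, fitted as written.** The true variance is (1 + rho) times the assumed one, so type I error = 2 × [1 − Φ(1.96/sqrt(1 + rho))]. This gives 11.0%, 13.3% and 14.4% at rho 0.5, 0.7 and 0.8, and 7.4% to 15.5% over rho 0.2 to 0.9. If the 6-month visit were a third level of time, (1 + 2 rho) replaces (1 + rho) and the range for rho 0.5 to 0.8 becomes 16.6% to 22.4%.

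**4. Simulation.** With 10,000 data sets per setting, 80 per arm and the ordinary F tests, the interaction rejected in 0.57%, 0.05% and 0.00% of null data sets at rho 0.5, 0.7 and 0.8, and the group term in 10.5%, 13.7% and 14.4%. This agrees with the formulas.

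**The case against.** The strongest reply is that the wording is shorthand. A mixed (split-plot) ANOVA is often described by exactly these factors, with the resident understood as the unit. The sentence speaks of changes and of a time factor measured on the same residents, and a condensed article may leave the error term to an analysis plan. This stands in part: the text does not prove that the subject term will be left out, and every figure above is conditional on a literal fit. But the article does more than stay silent. It names the method and lists its factors, and the method so named has the wrong error term for these data. Under either reading the same short correction settles it.

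Three further points stand:

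- No correlation is given in the documents, so the sizes are illustrative. Only the direction holds for every positive value.
- The t and Mann-Whitney comparisons, used at one time point or on change scores, need no subject term. The sample size rests on such a comparison, so the trial as a whole does not lose its planned power.
- The loss is smaller with 80 per arm than with 64.

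A reader might infer that the trial runs an 11-14% risk of a false claim of benefit. The documents do not support that. The figure belongs to the group main effect under an assumed correlation, and nothing in the article says that term will be used to judge efficacy. On the interaction the error is in the conservative direction.

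**Conclusion.** The point holds as a conditional one. The ANOVA as worded has no resident term although its time factor is repeated on the same residents. Fitted that way, its treatment test is too conservative for any positive within-resident correlation. With the plan's SD and effect and an assumed correlation of 0.5 to 0.8, power falls below the planned 80% at both sample sizes, while a within-resident error term keeps it above 80% throughout. The liberal group main effect is a secondary matter, to be closed off by saying that it is not interpreted. The point does not show that the analysis will be run this way, and it does not touch the simpler between-group tests.

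The same sentence also needs its time factor put right: it promises analyses at 6 weeks and 6 months, but time has only baseline and 6 weeks as levels, so the 6-month analysis has no place in the stated model.

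**What to change.** In Statistical methods:

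- Replace the two-way ANOVA with a repeated-measures (mixed) model: group as the between-resident factor, time as the within-resident factor, and a subject effect or an unstructured covariance.
- State that the group-by-time contrast is the treatment effect and that the group main effect is not interpreted.
- Make the levels of time match the stated analyses, by including the 6-month visit as a level or by giving a separate contrast for each follow-up time.

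This costs a few lines of wording. It uses data already planned for collection and changes neither the sample size nor any visit.

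### The two-way ANOVA announced for 6 weeks and 6 months has no 6-month level, and neither it nor the competing t or Mann-Whitney test adjusts for the baseline score

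*Protocol article*

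**What the plan says.** The Statistical methods section of the protocol article gives the quantitative outcomes two analyses.

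- Its first paragraph tests each outcome "using the 't' test, Mann-Witney test or the Chi-square test, depending on the type of outcome" and places the final analysis at both 6 weeks and 6 months from randomisation.
- Its second paragraph, on how body balance and muscle performance change, says that these changes "will be analysed 6 weeks and 6 months after starting the study using a two-way analysis of variance (ANOVA", and then defines the model: a group factor, "and the time (at baseline and after six weeks of intervention), and the interaction between them".

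Body balance is the primary outcome, so both paragraphs apply to it. Neither analysis is called primary. No subject or repeated-measures term is mentioned.

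The Sample size section plans for the 6-week comparison only, "assuming a difference of 5 points (SD 10) between the groups in the Tinetti test at the end of intervention", with "a two-sided alpha level of 0.05" and "a statistical power of 80%, and 20% of losses".

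**The concern.** Adjacent sentences disagree. One promises an ANOVA result at 6 weeks and at 6 months; the next builds a time factor from baseline and six weeks alone. A model with those two levels has no parameter for the 6-month visit. The Discussion presents longer follow-up as an advance on earlier trials, so that visit matters.

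The baseline score is collected from everyone but used inefficiently in one analysis and not at all in the other. In the ANOVA it is a level of the outcome, so the effect is a difference in change scores. In the t or Mann-Whitney comparison of follow-up scores it plays no part. What is at stake is precision that the trial has already paid for.

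With two analyses of the primary outcome and none designated, the results may differ and the choice could be made after the data are seen.

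**Working it through.** **Inputs.** From the Sample size section: difference 5, SD 10, two-sided alpha 0.05, power 80%, losses 20%, 160 in total. Assumed, because the article does not give it: the baseline-to-follow-up correlation rho, shown at 0.3, 0.5 and 0.7. Also assumed: the same SD at both times.

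**Step 1: reproduce the plan's figure.** The normal approximation gives 2 × (1.960 + 0.842)² × (10/5)² = 62.8, so 63 per arm; 63/0.8 = 78.75, so 79 per arm and 158 in total. The t-distribution version gives 63.77, so 64 per arm; 64/0.8 = 80 per arm, 160 in total. The stated size is reproduced. It rests on a plain two-group comparison of scores at the end of the intervention, not on the ANOVA. The steps below use 64 per arm.

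**Step 2: what the ANOVA contains.** Two groups by two times (baseline, 6 weeks) make four cell means. None of them is a 6-month mean, so no contrast of them gives a 6-month effect.

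**Step 3: standard errors at 6 weeks.**

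- Follow-up score (t test): 10 × √(2/64) = 1.768.
- Change score, which is the interaction in a repeated-measures ANOVA: 1.768 × √(2(1 − rho)).
- ANCOVA on baseline: 1.768 × √(1 − rho²).
- Variance ratio, change score to ANCOVA: 2(1 − rho)/(1 − rho²) = 2/(1 + rho).
- Power: Φ(5/SE − 1.960).

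| | rho 0.3 | rho 0.5 | rho 0.7 |
|---|---|---|---|
| SE, t test | 1.768 | 1.768 | 1.768 |
| SE, change score | 2.092 | 1.768 | 1.369 |
| SE, ANCOVA | 1.686 | 1.531 | 1.262 |
| Variance ratio, change score to ANCOVA | 1.54 | 1.33 | 1.18 |
| Power, t test | 81% | 81% | 81% |
| Power, change score | 67% | 81% | 95% |
| Power, ANCOVA | 84% | 90% | 98% |
| ANCOVA interval width relative to t test, √(1 − rho²) | 0.95 | 0.87 | 0.71 |

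The change score beats the t test only where 2(1 − rho) < 1, that is, where rho exceeds 0.5. ANCOVA beats the change score at every rho below 1 and the t test at every rho other than zero.

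**Step 4: simulation check, 5000 runs, rho 0.5 and 0.7.** Type I error was 4.9% and 5.2% for the repeated-measures interaction and 4.5% and 4.8% for ANCOVA. Power was 80.5% and 95.1% for the interaction, 89.4% and 97.6% for ANCOVA, and 79.6% and 79.8% for the t test. This agrees with the table.

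**Step 5: conditional case only, an ANOVA run with independent errors.** The interaction SE would be taken as √(4 × 10²/64) = 2.50, whatever rho is.

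- Type I error is 2 × (1 − Φ(1.960 × 2.50/true SE)): 1.9%, 0.6% and 0.03% at rho 0.3, 0.5 and 0.7.
- Power is Φ((5 − 1.960 × 2.50)/true SE): about 52%, 52% and 53%.

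Such a test would be conservative. In simulation it rejected a true null in 0.3% of runs at rho 0.5 and in almost none at rho 0.7.

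**The case against.** A reader might infer several stronger criticisms that the document does not support.

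- **That the ANOVA treats a person's scores as independent.** The article does not say so. Group, time and their interaction is also the usual description of a repeated-measures ANOVA, and a condensed article may leave the error term to the full plan. Step 5 is therefore a conditional warning, not a description of the plan.
- **That the ANOVA cannot give a valid estimate.** Under randomisation with complete data, the interaction is unbiased for the 6-week effect. Run as repeated measures, its test keeps its level. Even with independent errors the point estimate is unchanged and only its standard error is wrong.
- **That the treatment effect is halved, because the group main effect averages in the baseline scores.** The article never names the main effect as the efficacy test. It speaks of changes and includes the interaction, which is the natural contrast.
- **That the 6-month visit goes unanalysed.** The t, Mann-Whitney or chi-square tests are scheduled there too.

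Two further defences have weight. The sample size reproduces as a t-test calculation for the Tinetti score, so the powered comparison can be identified. That comparison is also valid at its planned power, which makes baseline adjustment a gain in efficiency rather than the repair of an error. At rho 0.3 the gain is small.

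These defences narrow the point but leave its core. The announced scope and the time factor still contradict each other. The sizing basis is not a statement of which analysis is primary. If the interaction were chosen, power would be below the planned 80% whenever rho is under 0.5 (67% at 0.3).

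**Conclusion.** The point holds in limited form. The contradiction over the 6-month visit is on the face of the text and needs no assumption, as is the absence of a designated primary analysis between the two given. The efficiency loss follows algebraically from using baseline as an outcome level or not at all.

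Its size depends on rho, which the article does not report, on equal SDs at both times, and on the plan's own difference and SD taken at face value with 64 completers per arm. The variance and width ratios do not depend on the difference, the SD or the number analysed; the power figures do.

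This should be corrected before analysis. It does not show that the planned tests are invalid or that the 6-month data would be ignored.

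**What to change.** Replace the two overlapping descriptions for quantitative outcomes with one named primary analysis. Either form will do, but one must be chosen:

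- ANCOVA of the 6-week score on group and baseline score, with the same model at 6 months; or
- a mixed model with 6 weeks and 6 months as repeated outcome levels, baseline as covariate, a group-by-visit term and within-person correlation.

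State that 6 weeks is the primary time point, in line with the Sample size section. Report the adjusted difference with its 95% confidence interval at each visit. Remove baseline from the levels of the time factor. Keep the t or Mann-Whitney tests as supportive.

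If the ANOVA is retained in any role, make its time factor agree with the visits it is said to cover and state the within-person term.

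The cost is wording only. Baseline is already measured under the Follow-up section, and no participant, visit or measurement is added.
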